**Results:**

The trial commenced in September 2025 and is currently in the recruitment and data collection phase. Participant enrollment is ongoing. Data collection is anticipated to be completed by July 2026, and findings from the study are expected to be disseminated through a peer-reviewed publication by December 2026.

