### Recruitment and Sampling

Participants will be recruited from the community through a multipronged strategy combining online and offline dissemination. This will include social media outreach, online announcements, and dissemination of posters in colleges, workplaces, and community locations. The inclusion criteria for the study are individuals aged 18 years and older, of all genders, fluent in English or Kannada, with at least 10 years of formal education, comfortable using a smartphone, experiencing self-reported current depressive or anxiety symptoms for 2 weeks or longer, and scoring 20 or above on the Kessler Psychological Distress Scale (K10) [25]. Participants will be excluded if they are currently receiving pharmacological treatment for any mental health condition, have attended 3 or more psychotherapy or counseling sessions in the past 3 months, or are presently engaged in counseling or psychotherapy. Individuals currently using any other mental health app, or those not amenable to participating in the study as assessed in a brief telephonic interview, or those having significant suicidal ideation as determined by responses on 2 items pertaining to the frequency and controllability of suicidal thoughts in the past 1 month, will be excluded from the study.

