### Procedure

Participants will be randomized into either the intervention or control group in a 1:1 ratio, using a computer-generated randomization sequence. The randomization list will be generated by the study supervisor. Stratified randomization will be used based on age group (18-35 years and 36 years and above) and gender to ensure balance across key demographic variables.

A brief telephonic interview for eligibility screening will be conducted after all other questionnaires are completed. This call allows the researchers to clinically assess the current mental state and amenability to take part in the study process, inquire whether participants have sought consultation for any psychiatric problem in the past or recent times, and confirm willingness to participate.

Eligible participants will receive an introductory call informing them of their group allocation and guiding them on how to begin engagement with the study activities. All assessments will be conducted through an online survey, and feedback will be obtained over the phone from both groups at the end of the 4-week intervention period. A follow-up telephonic interview will be conducted 1 month after the postintervention assessment to ascertain help-seeking inclination and help-seeking behavior. The flow of the study is depicted in Figure 1.

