Suicidal ideation—2 brief items developed for the study will be used to determine significant suicidality based on frequency and controllability. This is for screening out those who may need immediate support and referral. The first item asks, “In the past month, how often have you had thoughts about suicide?” with response options ranging from never (coded as 1), rarely or 1-2 times (coded as 2), sometimes (coded as 3), often (coded as 4), and all the time (coded as 5). The second item asks, “When feeling very sad or emotionally distressed, and thoughts of self-harm or suicide arise, how much control do you feel you have over acting on these thoughts?” Responses are rated as able to control easily (coded as 1), able to control with some difficulty (coded as 2), able to control with great difficulty (coded as 3), not able to control (coded as 4), and not applicable—do not experience such thoughts (coded as 5). All participants who report rarely having suicidal thoughts with great difficulty or no control; those who report sometimes having suicidal thoughts with great difficulty or no control, or those reporting often having suicidal thoughts, regardless of how much control they report, will be excluded.

Help-seeking inclinations will be assessed through the use of the General Help-Seeking Questionnaire (GHSQ). This 14-item scale will be used to assess the likelihood of seeking help from various sources (eg, parents, friends, helpline, and mental health professionals) for current mental health concerns or psychological distress, on a 7-point Likert scale [32]. Ratings on the item specific to mental health professionals will be the primary focus, although help-seeking inclination from various sources will also be documented. At follow-up, for the sake of minimizing respondent burden, help-seeking inclination only from mental health professionals will be assessed using the corresponding GHSQ items with a 7-point Likert-type scale.

The Barriers to Seek Professional Help for Mental Health Scale (BSPH-MHS) will be used to assess the severity and nature of perceived barriers to professional help-seeking for mental health concerns or psychological distress. It is a 28-item, 5-point Likert scale that evaluates perceived barriers across 4 domains: distress perception, stigma, service apprehensions, and instrumental obstacles with previous research supporting its reliability, construct, and convergent validity [30].

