Only authorized research team members will have access to identifiable data. WhatsApp messages will be standardized and delivered via a business account, with no sensitive information exchanged. Referral-related guidance to seek appropriate professional help will be provided for all individuals who are not eligible for participation and those who decline participation. Participants will receive appropriate mental health service suggestions based on their needs and preferences at any point in time if required. Participants will be free to opt out of the study at any point. A telephone session will be held with those who score above the cutoff on suicidality to guide, motivate, and support them in seeking professional help. They will not be part of the study. Helpline numbers are also available in the app and will be shared with these individuals for use as per their needs. These individuals will also be informed that they can reach out to the researcher again if they need more referral options at a later point. The active control group will be debriefed at the end of the study and provided information and links to the MindNotes app. In addition, they will be free to contact the researcher for guidance or professional help at any point during the intervention period, if they so desire.

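### The suicidality exclusion rule leaves out the highest frequency answer, *all the time*, although it excludes *often* at every level of control

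*Protocol article*

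**What the plan says.** The Data Collection Instruments section describes two items written for this study. The first asks how often the person has had suicidal thoughts in the past month. Its options start at *never* (1) and *rarely* (2) and continue "sometimes (coded as 3), often (coded as 4), and all the time (coded as 5". The second asks how much control the person has over acting on such thoughts: easy control (1), some difficulty (2), great difficulty (3), no control (4), or not applicable (5).

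The purpose is given in the same section: "This is for screening out those who may need immediate support and referral". The rule then lists its cases by name. *Rarely* and *sometimes* lead to exclusion when combined with great difficulty or no control. The last clause is "those reporting often having suicidal thoughts, regardless of how much control they report, will be excluded".

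Three other sections bear on the point:

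- Recruitment and Sampling excludes "those having significant suicidal ideation as determined by responses on 2 items", without naming response levels.
- Procedure describes a telephone eligibility interview: "This call allows the researchers to clinically assess the current mental state and amenability to take part in the study process".
- Ethical Considerations promises a supportive telephone session to "those who score above the cutoff on suicidality".

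The abstract reports that recruitment has begun: "Participant enrollment is ongoing".

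**The concern.** A screening rule for suicidality should not become more lenient as the thoughts become more frequent. Here it does so at the top of the scale. *Often* excludes whatever the answer on control, but *all the time* is not mentioned in the rule at all.

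The trial recruits adults with a K10 score of 20 or above who are not in treatment, so an answer in the top category is plausible. If the screening form or the eligibility check was built from this sentence, a person reporting constant suicidal thoughts could be randomized to a minimally guided app or to mood logging. That person would also not be covered by the support call that excluded respondents receive. The issue is participant safety. It does not bear on the estimate of the treatment effect.

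**Working it through.** The plan gives no figure to reproduce here. The check applies the written rule to every possible pair of answers.

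**Inputs** (all from Data Collection Instruments). Frequency *f*: never 1, rarely 2, sometimes 3, often 4, all the time 5. Control *c*: easy 1, some difficulty 2, great difficulty 3, none 4, not applicable 5.

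**Rule as written.** Exclude if (*f* is 2 or 3, and *c* is 3 or 4), or if *f* = 4.

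**Rule with the top category added.** Exclude if (*f* is 2 or 3, and *c* is 3 or 4), or if *f* is 4 or 5.

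| Frequency | Control answers that exclude, as written | Pairs excluded, as written | Pairs excluded, corrected |
|---|---|---|---|
| Never (1) | none | 0 of 5 | 0 of 5 |
| Rarely (2) | 3, 4 | 2 of 5 | 2 of 5 |
| Sometimes (3) | 3, 4 | 2 of 5 | 2 of 5 |
| Often (4) | 1 to 5 | 5 of 5 | 5 of 5 |
| All the time (5) | none | 0 of 5 | 5 of 5 |

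Totals: 0 + 2 + 2 + 5 + 0 = 9 of 25 as written, and 0 + 2 + 2 + 5 + 5 = 14 of 25 corrected.

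Some of the 25 pairs contradict themselves, such as *often* with *not applicable*. Dropping *never* and *not applicable* leaves 4 × 4 = 16 pairs. As written, 2 + 2 + 4 + 0 = 8 of 16 are excluded; corrected, 2 + 2 + 4 + 4 = 12 of 16.

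The clearest contrast is in the *no control* answer. It excludes at *rarely*, *sometimes* and *often*, but not at *all the time*.

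**Does another section repair the rule?**

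- Recruitment and Sampling refers back to the two items and adds no threshold.
- Procedure gives the interview a general clinical purpose but no suicidality criterion.
- Ethical Considerations speaks of a cutoff, but none is defined anywhere as a number. A summed score could not serve: *never* with *not applicable* gives 1 + 5 = 6 and is not excluded, while *rarely* with great difficulty gives 2 + 3 = 5 and is. The word can therefore only stand for the case-by-case rule, and it carries the same gap.

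**The case against.** The strongest reply is that nobody would apply the sentence literally. Someone who has such thoughts all the time also has them often in ordinary speech, the stated purpose of the items points one way, and the reference to scoring above a cutoff suggests an ordered threshold with code 5 above code 4. There are also other safeguards. The telephone interview follows the questionnaires and assesses mental state, and lack of amenability at that interview is an exclusion criterion of its own. Service suggestions are offered to participants when required. The MindNotes app has a crisis section with helpline numbers. Finally, the counts of answer pairs say nothing about how many people are affected.

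Much of this stands. The intent is almost certainly to exclude *often* and above, the form in use may already be right, and the interview lowers the practical risk. The pair counts describe the shape of the rule and are not a measure of harm.

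What does not follow is that the text can stay. The rule is written case by case against labelled response options, so *often* is the name of one answer and not a loose description. The interview is a clinical judgement with no stated suicidality threshold. Service suggestions and helpline numbers are support and do not decide eligibility, and the control arm is given access to MindNotes only after the study ends. None of these settles what happens to a code 5 answer.

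**Conclusion.** The rule is wrong as written. It excludes 9 of 25 answer pairs where 14 are evidently intended, and the five missing pairs are exactly those with the most frequent suicidal thoughts. The support call has the same gap.

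This conclusion rests on reading the response labels literally, as a form or checklist would apply them. It does not show that any high-risk person has been enrolled, and the number affected cannot be derived from the document. Nothing changes for the primary outcome, the sample size or the analysis. Because this is an eligibility and safety rule in a trial that is already recruiting, it must be corrected.

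**What to change.** 1. In Data Collection Instruments, insert *or all the time* after *often* in the last clause of the exclusion rule, so that both answers exclude at every level of control.
2. In Ethical Considerations, replace the undefined cutoff with a reference to that rule, so that everyone it excludes is offered the support call.
3. Check how the screening form in use handles the *all the time* answer, and check the records of participants already enrolled for it. Anyone found should be offered the support call now.

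The cost is one clause, one cross-reference, and a check of one item in the form and the records. No procedure is added to the trial.

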### Feedback Items

Feedback items at the postintervention assessment will include ratings on the current severity of distress on a 5-point Likert-type scale, frequency of using the app in the previous 1 month (multiple-choice item), challenges in using the app regularly or frequently (open-ended item), ease of navigation, relevance, and usefulness of the content of the intervention (5-point Likert-type items). Perceived benefits of participating in the study will be assessed using a set of 10-point Likert-type items on improvements in knowledge about common mental health concerns and seeking professional consultation for mental health, reduction in hesitations to consult a mental health professional when needed, and improvement in motivation to consult a mental health professional relative to baseline. The likelihood of recommending the intervention to others who may be distressed but not seeking professional help will also be assessed using a 10-point Likert-type item. In addition, an open-ended question will be used to document the impact of participating in the intervention, if any.

An overview of enrollment, interventions, and assessments is provided in Figure 2.

**Figure 2 figure2:**
[figure not shown]
SPIRIT (Standard Protocol Items: Recommendations for Interventional Trials) diagram outlining the schedule of enrollment, intervention, and assessment. Suicidal ideation is assessed using 2 items developed by the researchers. The follow-up assessment includes only the General Help-Seeking Questionnaire (GHSQ) items assessing help-seeking inclination towards mental health professionals; this is indicated as “Xa”. BSPH-MHS: Barriers to Seek Professional Help for Mental Health Scale; HSB: help-seeking behavior; K10: Kessler Psychological Distress Scale.

### Ethical Considerations

The study has been approved by the Institutional Ethics Committee of the National Institute of Mental Health and Neurosciences, Behavioural Science Division (NIMHANS/45th IEC [BEH.SC.DIV.]/2024/22.03.2024) and is prospectively registered in the Clinical Trials Registry of India. Informed consent will be obtained from individuals prior to recruitment, and no compensation will be offered to participants for taking part in the study. Baseline and postintervention surveys will be administered electronically via REDCap (Research Electronic Data Capture), a secure, web-based platform for data collection and management, hosted at the first author’s institution. The digital apps used in the study incorporate “privacy by design” and use technical and policy safeguards to ensure the security of the data and protect the privacy of users. User passwords are stored securely through encryption. Personally identifiable information elements (email addresses and phone numbers) are stored in encrypted form and are decrypted within the program when needed. The data obtained from the participants through text messages and emails will be backed up and stored on a password-protected system.

Only authorized research team members will have access to identifiable data. WhatsApp messages will be standardized and delivered via a business account, with no sensitive information exchanged. Referral-related guidance to seek appropriate professional help will be provided for all individuals who are not eligible for participation and those who decline participation. Participants will receive appropriate mental health service suggestions based on their needs and preferences at any point in time if required. Participants will be free to opt out of the study at any point. A telephone session will be held with those who score above the cutoff on suicidality to guide, motivate, and support them in seeking professional help. They will not be part of the study. Helpline numbers are also available in the app and will be shared with these individuals for use as per their needs. These individuals will also be informed that they can reach out to the researcher again if they need more referral options at a later point. The active control group will be debriefed at the end of the study and provided information and links to the MindNotes app. In addition, they will be free to contact the researcher for guidance or professional help at any point during the intervention period, if they so desire.

### Data Analysis Plan

Quantitative analyses will be conducted using SPSS Statistics (version 31.0; IBM Corp). Baseline characteristics will be summarized descriptively. Differential attrition will be examined by comparing dropout rates between groups using chi-square tests and by assessing baseline differences between completers and noncompleters using appropriate statistical tests. Sensitivity analyses will be conducted as needed based on the observed pattern of missing data.

Occurrence of professional help-seeking at the postintervention assessment and follow-up will be compared between groups using proportions, chi-square tests, and odds ratios with 95% CIs, with Cohen *h* reported as the effect size. As this behavioral outcome has no baseline variation in the nontreatment-seeking study sample, this will be treated as a completer analysis involving participants who provided postintervention assessment data.

For continuous outcomes, linear mixed-effects models will be used to estimate group, time, and group×time effects under an intention-to-treat framework. In addition, completer-only analyses will be conducted as exploratory comparisons to describe observed change among participants with complete data. A 2-sided significance level of .05 will be used.

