### Objectives

The objectives of the study are to evaluate the effectiveness of the minimally guided MindNotes app in enhancing professional help-seeking behaviors among individuals with self-reported common mental health concerns and significant psychological distress who are not currently engaged in treatment. Additionally, the study aims to examine the utility of this app in improving the inclination to seek help from mental health professionals, reducing perceived barriers to seeking professional help for mental health, reducing psychological distress, and documenting perceived benefits of using the app. Help-seeking behavior is the primary outcome variable, while help-seeking inclination, barriers to seeking professional help, and psychological distress are the secondary outcome variables.

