### Power Calculation

A sample size of 150 participants per group has been estimated based on detecting a difference in help-seeking behavior (25% vs 10%) with 80% power at a 5% significance level using G*Power 3.1, allowing for up to 33% attrition commonly observed in minimally guided digital interventions [26]. These include interventions delivered through digital platforms, which often vary widely in design and outcomes. Consequently, closely comparable studies for precise sample size estimation were difficult to identify, and the current estimate is informed by findings from studies with broadly similar characteristics [14,27].

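### The primary help-seeking comparison ignores the age and gender strata used at randomisation; if those factors predict help-seeking, the crude test is slightly conservative and loses a little power

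*Protocol article*

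**What the plan says.** The Procedure section of the protocol article describes 1:1 allocation and says: "Stratified randomization will be used based on age group (18-35 years and 36 years and above) and gender". The stated purpose is "to ensure balance across key demographic variables".

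The Objectives section says: "Help-seeking behavior is the primary outcome variable". The outcome is a single yes/no item. The Data Analysis Plan fixes its comparison at postintervention and follow-up: "using proportions, chi-square tests, and odds ratios with 95% CIs", with Cohen h as effect size, in participants who supplied postintervention data. Neither stratification factor enters this comparison. The error rate is also fixed: "A 2-sided significance level of .05 will be used".

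The Power Calculation section rests on "detecting a difference in help-seeking behavior (25% vs 10%) with 80% power at a 5% significance level using G*Power 3.1", and arrives at 150 per group after allowing for attrition of up to 33%.

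**The concern.** When arms are balanced by design on a factor that predicts the outcome, chance differences between arms on that factor are largely removed. The ordinary chi-square still counts that variation in its standard error. The standard error is then too large, the P value leans towards non-significance, and some power goes unused. An analysis that conditions on the strata restores the match between design and test.

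The second issue is the analysis set. Stratification balances those randomised, but the primary comparison uses completers. If dropout depends on age or gender differently in the two arms, the balance is lost and the crude comparison has no protection. An analysis that includes the two factors does.

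The plan names a specific test for the primary outcome, so this is not a detail left for a fuller document to supply.

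**Working it through.** **1. The plan's sample size.** Inputs from the Power Calculation section: 25% vs 10%, two-sided 5%, 80% power, 33% attrition. The mean rate is 0.175.

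- n = [1.96·√(2·0.175·0.825) + 0.8416·√(0.25·0.75 + 0.10·0.90)]² / 0.15² = (1.0532 + 0.4433)² / 0.0225 = 99.5, so 100 evaluable per arm.
- 100 / (1 − 0.33) = 149.3, so 150 per arm. This matches the article.
- Power at 100 per arm is 80.2%.

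The figure belongs to an unadjusted two-proportion test without continuity correction, so sample size and stated test agree with each other.

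**2. Size of the effect under random attrition.** The article gives no association of age or gender with help-seeking, no stratum sizes and no blocking scheme. The following are therefore assumptions: four strata with shares 35/35/15/15%, blocks of 4, the same odds ratio for each factor, a common treatment odds ratio within strata, and 33% attrition at random and equal between arms. Each cell has 200,000 simulated trials with 300 randomised. The Pearson chi-square without correction is compared with the Cochran-Mantel-Haenszel (CMH) test.

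| Assumed OR per factor | Crude alpha, common rate 10% | Crude alpha, common rate 17.5% | Power at 25% vs 10%: crude | Power: CMH | Difference (points) |
|---|---|---|---|---|---|
| 1 | 0.050 | 0.051 | 81.4% | 81.0% | −0.4 |
| 1.5 | 0.050 | 0.050 | 81.4% | 81.4% | 0.0 |
| 2 | 0.048 | 0.047 | 81.7% | 82.3% | +0.6 |
| 3 | 0.045 | 0.044 | 82.1% | 84.1% | +2.0 |
| 5 | 0.042 | 0.039 | 82.7% | 87.0% | +4.3 |

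CMH alpha is 0.049-0.050 throughout. Monte Carlo error is about 0.0005 on alpha and 0.001 on power.

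**3. Analytic check.** If the strata explain a share R² of the outcome variance and balance is exact, actual alpha = 2·[1 − Φ(1.96/√(1 − R²))]. For an odds ratio of 2 per factor and an overall rate of 17.5%, the stratum rates are 18.5/10.2/31.2/18.5% and R² is 0.033. Then 1.96/√0.967 = 1.993 and alpha = 0.046, close to the simulated 0.047.

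**4. Attrition that differs by arm and stratum.** This is an illustration with assumed inputs: no treatment effect, average rate 15%, 150 randomised per arm, and the same stratum shares. Completion by stratum is 75/65/65/50% in control and 60/70/70/80% in the app arm.

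- Overall completion is 0.35·0.75 + 0.35·0.65 + 0.15·0.65 + 0.15·0.50 = 66% in control and 0.35·0.60 + 0.35·0.70 + 0.15·0.70 + 0.15·0.80 = 68% in the app arm. The planned comparison of dropout rates would rarely flag this.
- False positives favouring the app (nominal 2.5%), crude vs CMH: 3.6% vs 2.6% at OR 1.5 per factor, 4.4% vs 2.4% at OR 2, and 5.6% vs 2.4% at OR 3.
- The spurious crude difference is about 1.3 points at OR 2 and 2.1 points at OR 3.

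The pattern was chosen to show the mechanism. Nothing in the article says how likely it is.

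**5. The estimand.** Rates of 25% vs 10% give a crude odds ratio of (0.25/0.75)/(0.10/0.90) = 3.00. The within-stratum odds ratio that produces the same rates is 3.11 at OR 2 per factor, 3.28 at 3 and 3.65 at 5. The adjusted and crude odds ratios are different quantities.

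**The case against.** The strongest reply is that nothing in the plan is invalid. A crude chi-square after stratified randomisation does not inflate type I error when attrition is random, and the trial was sized for exactly this test. The stated reason for stratifying is demographic balance, not power. Crude power stays above the planned 80% in every scenario in the table. All of this stands, and it keeps the point minor.

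The two arguments for adjustment also rest on different conditions. Conservatism needs balance to persist among completers, whereas protection against imbalance matters when it does not. This is correct, but a stratified analysis serves in either case, and the trial cannot know in advance which will apply.

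Three stronger readings are tempting, and the article does not support them:

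- A reader might infer that the primary test is certainly conservative. That requires age or gender to be prognostic and balance to hold among completers, and the article gives figures for neither.
- A reader might infer that adjustment makes the odds ratio more precise. An adjusted logistic odds ratio is conditional, and its standard error is usually not smaller. Any gain lies in the power of the test or in a standardised risk difference.
- A reader might infer that the mixed models are misspecified because only group, time and their interaction are listed. Those are the effects to be estimated. A condensed article may leave covariates to a fuller plan.

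**Conclusion.** The point holds as a minor improvement to the primary binary analysis. Design and test do not match, and under random attrition any cost is towards caution: negligible for odds ratios up to 2 per factor, about 2 power points at 3, and about 4 at 5. With no association, the stratified test is about 0.4 points worse, so the change is nearly but not entirely free. These sizes rest on assumed associations, stratum shares and blocking, not on figures in the article.

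A reader might go further and conclude that the trial is underpowered or its false-positive rate uncontrolled. Neither follows. The sample size reproduces exactly, and inflation appears only in a constructed attrition pattern that differs by arm and stratum. In that setting adjustment removes only the bias that runs through age and gender. It does not cure other missingness.

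**What to change.** Prespecify one stratified primary analysis for help-seeking, before outcomes are compared by arm:

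- either a Cochran-Mantel-Haenszel test over the age-by-gender strata, with a rule for pooling very small gender cells;
- or a logistic regression on arm, age group and gender, reported with a standardised risk difference and 95% CI.

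State that the adjusted odds ratio is conditional and not directly comparable with the crude one. Keep the crude chi-square and odds ratio as supportive. Adding age group and gender to the mixed models is optional, for consistency.

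The cost is wording. Both factors are known for everyone randomised, the planned software fits either analysis, and the sample size does not change. The article expects data collection to run to July 2026. A choice fixed before the results are seen cannot be called data-driven.
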